## Methods/Design

### Aims

The PALM cohort study will establish and follow-up a cohort of mother-child pairs who had a prenatal diagnosis of a CNV from 2013-2019 (inclusive) in the Australian state of Victoria. Victoria has approximately 78,000 births per year and a median maternal age of 31.5 years [13]. Approximately 2-3% of all pregnant women undergo prenatal diagnosis per year [14].

The study aims are to:
Compare the developmental, social-emotional and health status of children with a prenatal diagnosis of a prenatal CNV with those children with no CNV detected on CMA.Measure the impact of a prenatal diagnosis of a CNV on maternal perceptions of child health, behavior, and development.Determine the proportion of CNV ascertained prenatally that are reclassified from unknown or uncertain to benign or pathogenic after two or more years using contemporaneous curation resources.

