### Study population

Each year the VPDD receives prenatal diagnostic testing results on approximately 150 pregnancies with CNVs, and 1000 pregnancies with no CNVs. We will recruit an equal number of participants with and without CNVs, frequency matched for fetal sex, trimester at prenatal diagnosis, maternal age group (by decade) and calendar year of testing. Due to the modifier of structural anomaly on childhood outcomes, women with fetal structural abnormalities will be excluded from the control group of pregnancies with no CNVs.

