### Inclusion criteria

The biological mother (gestational carrier) is the most relevant parent/legal guardian to consent for participation as she was the individual that underwent the prenatal diagnostic procedure. She will be eligible by meeting the following criteria:
Prenatal CMA result reported in a singleton pregnancy during January 2013 - December 2019 inclusiveAt least 18 years of age at enrolmentAble to provide informed consent in EnglishLive infant outcome from index pregnancyPrimary care-giver for the child at the time of hospital discharge after birthCapable of providing consent on behalf of herself and her childAble to complete the parental questionnaires and accompany her child for study assessmentsResides in Victoria

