### Data collection

Child outcome data will be collected via parent-completed quantitative surveys using validated measures and through psychologist and/or pediatrician assessment. See Table 2 for an overview of study instruments used for each outcome measure. The study data will be collected in 5 main forms.
Parent-completed questionnaires – off-site, in parent’s own timeVineland Adaptive Behavior scale (VABS) – telephone interview with mother conducted by a study psychologistWPPSI-IV – child assessment conducted on-site by a study psychologist at the Melbourne Children’s Trials Centre, Parkville, MelbourneClinical assessment by study pediatrician – conducted on-site at the same visit as the WPPSI-IV wherever practicable.Laboratory reanalysis of the prenatal CNV result - no interview or participant attendance required.

**Table 2 Tab2:** Overview of study instruments used in the PALM study for children aged 12 months to 7 years

Data collection method	Time point	Instrument	Completed by	Delivery and time
**Outcome 1:** To compare the developmental, social-emotional and health status of children with a prenatal diagnosis of a prenatal copy number variant with those children with no copy number variant detected on chromosomal microarray.				
Quantitative survey	Children aged 12 months or older.	Brief Infant-Toddler Social and Emotional Assessment (BITSEA) [20]	Parent	Online or hard copy. 30-40 minutes total
		Strengths and Difficulties Questionnaire (SDQ) [21]	Parent	
		Maternal Postnatal Attachment Questionnaire (MPAS) [22]	Parent	
		Vulnerable Child Scale (VCS) [23]	Parent	
		Profile of Mood States (POMS) [24]	Parent	
		Parent Sense of Competence Scale (PSOC) [25]	Parent	
		Golombok Rust Inventory of Marital State (GRIMS) [26]	Parent	
		Disclosure of Results to Others [27]	Parent	
		Secrecy about Results [28]	Parent	
		Decision Satisfaction Scale [29, 30]	Parent	
		Revised Scale of Ambiguity Tolerance [31]	Parent	
		Genetic essentialism, general understanding of genetics and accuracy of understanding of results [32, 33]	Parent	
		Patient Health Questionnaire depression scale (PHQ-8)	Parent	
		Children with Special Health Care Needs (CSHCN) screener [34]	Parent	
**Outcome 2:** To measure the impact of a prenatal diagnosis of a copy number variant on maternal perceptions of their child.				

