#### For the 12–24-month-old group, the ASQ-3 and ASQ:SE-2 scores are the primary outcomes

Scores for individual items are summed to give an overall continuous score for each of the domains in the ASQ-3 and ASQ:SE-2. In addition to using scores as continuous outcomes, we will categorize the scores according to the recommended scores for typical development, need for monitoring, and need for further assessment. We will collapse these three categories into a binary variable (those with typical development vs those with a need for monitoring or further assessment [i.e., potential atypical or delayed development]). The differences in those with typical and ‘atypical’ scores will be compared among the CNV subgroup using chi-squared test for proportions or Fisher’s exact test as appropriate.

#### Objective 2

The primary outcome will be the BITSEA score. We will analyze the data according to the subgroup of CNV result (pCNV, VUS) compared with controls, stratified by age. The secondary outcomes will be the Maternal Postnatal Attachment Questionnaire (MPAS), Vulnerable Child Scale (VCS), Profile of Mood States (POMS), and the Parent Sense of Competence Scale (PSOC). For the secondary outcomes, we will compare group differences in responses using mixed effect regression models. We will report mean values for the parent report of child behavior, parenting competence, attachment, perceived child vulnerability and parent mood. Parent gender, country of birth, education, employment status, and child sex will be adjusted as covariates.

#### Objective 3

We will compare the classifications given at the time of issue of the prenatal report and the current classifications in 2020-21 according to the issuing laboratory’s protocols. The proportion of pCNVs, VUS and benign variants will be compared between the prenatal and 2-year postnatal classifications using chi-squared test for proportions.

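### The Objective 2 secondary-outcome model leaves out three of the four matching factors and adjusts for a parent gender that the design holds constant

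*Protocol article*

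**What the plan says.** Under Objective 2 in the statistical methods section, the protocol article names four secondary outcomes: MPAS, VCS, POMS and PSOC. It says "For the secondary outcomes, we will compare group differences in responses using mixed effect regression models", and then "Parent gender, country of birth, education, employment status, and child sex will be adjusted as covariates". No random effect or grouping unit is named. An earlier sentence in the same paragraph, placed after the BITSEA primary outcome, says that each CNV subgroup is compared with controls with stratification on age.

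Three other places bear on this:

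- **Study population:** the cohorts are to be equal in number and "frequency matched for fetal sex, trimester at prenatal diagnosis, maternal age group (by decade) and calendar year of testing".
- **Inclusion criteria:** "The biological mother (gestational carrier) is the most relevant parent/legal guardian to consent for participation". The same list requires her to be able to fill in the parental questionnaires. The second aim is to "Measure the impact of a prenatal diagnosis of a CNV on maternal perceptions of child health, behavior, and development".
- **Secondary outcomes of Objective 1:** the regression there is to account for modifiers and confounders, and maternal age is the first example given.

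**The concern.** The Objective 2 covariate list is closed, whereas the Objective 1 list is given by way of example. Of the four matching factors it keeps only child sex. Maternal age therefore counts as a confounder or modifier for child outcomes but not for scales of maternal mood, attachment and competence, where it is at least as plausible an influence.

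Matching would be a good answer if the whole CNV group were compared with controls. The plan instead makes two contrasts, VUS against controls and pathogenic CNV against controls, and the matching does not promise balance within either. If the subgroups differ in maternal age, trimester or year of testing, that difference passes unadjusted into the contrasts.

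The list also includes parent gender, in a study where the respondent is the biological mother. Either the covariate is misplaced, or other parents may respond. In the second case the inclusion criteria and the second aim no longer describe the data.

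**Working it through.** **1. Matching factors against covariates**

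| Matching factor (Study population) | In the Objective 2 list? |
|---|---|
| Fetal sex | Yes, as child sex |
| Trimester at diagnosis | No |
| Maternal age group, by decade | No |
| Calendar year of testing | No |

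**2. Planned numbers (Sample size section)**

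- VUS: 85 per year × 7 years × 45% = 267.75, given as 267.
- Pathogenic CNV: 62 × 7 × 20% = 86.8, given as 87.
- Controls: 7155 × 5% = 357.75, given as 358.
- CNV group: 267 + 87 = 354. All respondents: 354 + 358 = 712.

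The plan's own figures reproduce. It gives no power calculation for Objective 2, so there is no further figure to check.

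**3. What whole-group matching leaves in each contrast**

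Let a matching factor have mean V among VUS and P among pathogenic CNVs. Suppose matching works perfectly, so that controls have the mean of the pooled CNV group:

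C = (267/354)·V + (87/354)·P = 0.754·V + 0.246·P

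Then:

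- P − C = 0.754·(P − V)
- V − C = 0.246·(V − P)

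About three quarters of any subgroup difference remains in the pathogenic CNV contrast and one quarter in the VUS contrast. Both are zero only if the subgroups are alike on that factor. The documents report neither V nor P for any factor, so the size of P − V is unknown. The differing recruitment rates (20% and 45%) shift the mix: pathogenic CNVs are 62/147 = 42% of recorded CNVs but 87/354 = 25% of the planned cohort. The controls will therefore resemble the VUS group more closely.

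**4. Parent gender**

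In a simulated design matrix of 712 rows (intercept, group and four binary covariates), the rank is 6 with 6 columns. Adding a constant parent-gender column gives 7 columns and still rank 6. The group coefficient is 0.0710 in both fits. The term cannot be estimated, but it does not disturb the comparison.

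**5. The mixed model**

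Table 2 gives one time point for these scales ("Children aged 12 months or older") and describes no repeat wave. With one record per mother, a mother-level variance cannot be separated from the residual: on simulated data the log-likelihood is −1006.236 for variance splits 0.1/0.9, 0.5/0.5 and 0.9/0.1. A random intercept for recruiting source is different. With six simulated sources (five hospitals plus private and regional, an assumption), the model converged, with source variance 0.58 and residual variance 1.00.

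**The case against.** The strongest reply is that the design already controls the three omitted factors through matching, so that adjustment is a matter of precision. That holds for the CNV group as a whole. It does not hold for the two separate contrasts, for the reason in step 3.

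Several stronger readings are tempting, and the documents do not support them:

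- **That the random effects have nothing to attach to.** This is true only of a mother-level effect with one record each. The Pre-screening section describes five public units plus private and regional referrers, and eligibility is per singleton pregnancy with no stated limit of one per woman, so either could supply a grouping unit. A journal article may also leave the random-effect structure to the full protocol or analysis plan. That mothers are surveyed once is itself an inference from Table 2.
- **That child age is ignored.** The Objective 2 paragraph stratifies by age, and matching on year of testing roughly balances it. What remains is an ambiguity over whether that sentence reaches the secondary outcomes. If the Table 2 bands are the strata, the older one runs from 2 years 7 months to 7 years 7 months, so five years of age variation stay within it.
- **That parent gender damages the analysis.** It does not; the group estimate is the same without it.
- **That employment status is a consequence of the prenatal result and should leave the main model.** It is recorded after the result, but nothing in the documents shows that the result changed it.

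**Conclusion.** The point holds as a modest, low-cost correction. The closed list omits three of four matching factors, is inconsistent with the Objective 1 treatment of maternal age, and relies on matching that does not guarantee balance in the contrasts actually made. Under perfect whole-group matching at the planned numbers, the residual imbalance is 75% (pathogenic CNV) and 25% (VUS) of whatever difference exists between the subgroups. No bias is demonstrated, because that difference is not reported. The gain in precision cannot be sized either, because the documents do not say how much score variance these factors explain.

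Parent gender is a real contradiction with the inclusion criteria and the second aim, but a matter of coherence and of who responds. The unnamed random effect is an ambiguity to settle; it does not show that the model cannot be fitted.

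**What to change.** 1. Add maternal age, trimester at diagnosis and calendar year of testing to the Objective 2 models.
2. Adjust for child age at completion within the age strata, or state that the age stratification covers the secondary outcomes and define the strata. Check collinearity first: if questionnaires are completed within a short calendar window, child age and year of testing will be nearly the same variable.
3. Delete parent gender. If other parents may respond, reconcile this with the inclusion criteria and the second aim.
4. Use ordinary linear regression unless a grouping unit, such as recruiting site, is named for the random effect.

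The cost is a few sentences and no new data collection, since the three factors must be held for the matching. With maternal age linear (1), trimester as three levels (2) and seven calendar years as categories (6), the extra terms use 1 + 2 + 6 = 9 degrees of freedom. The smaller contrast, pathogenic CNV against controls, has 87 + 358 = 445 planned respondents. Entering year as a linear term would reduce the 9 to 4.

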Quantitative survey	‘Younger cohort’ children who are 12-30 months old at the time of enrolment	Ages and Stages Questionnaire-3	Parent	Online or hard copy. 20-30 minutes.
		Ages and Stages Questionnaire Social Emotional-2	Parent	
Quantitative survey	‘Older cohort’ children who are 2 years 7 months to 7 years 7 months at the time of enrolment	The Vineland-II Adaptive Behavior Scale (VABS)	Parent	Online or hard copy. 20-60 minutes
Psychologist assessment		Wechsler Preschool and Primary Scale of Intelligence IV (WPPSI-IV)	Psychologist	In person. 20-60 minutes
Clinical assessment		Clinical assessment by study pediatrician: measurements of height, weight, and head circumference; history and physical examination	Paediatrician	In person. 20-60 minutes
**Outcome 3:** The frequency of copy number variants that have a change in classification after reanalysis after ≥2 years will be presented in a descriptive analysis. For the participants in the reanalysis group, an additional letter will be sent to them with the results of the updated analysis.				
Clinical standard laboratory software and databases in use during 2021-2022	Children who were prenatally diagnosed with a copy number variant of uncertain or unknown significance	Affymetrix Chromosome Analysis Suite (ChAS) software	Cytogenetics Laboratory	n/a
		DatabasE of Chromosomal Imbalance and Phenotype in Humans using Emsembl Resources (DECIPHER)	Cytogenetics Laboratory	
		International Standards for Cytogenomic Arrays (ISCA) database	Cytogenetics Laboratory	
		Online Mendelian Inheritance in Man (OMIM)	Cytogenetics Laboratory	

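### Objective 3 gives two reading windows for the same reclassification, and the 2020-21 window does not ensure the stated two-year minimum for results reported in 2019

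*Protocol article*

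**What the plan says.** The Aims define the third objective as the proportion of CNVs "reclassified from unknown or uncertain to benign or pathogenic after two or more years using contemporaneous curation resources". Table 2, Outcome 3, repeats the minimum, describing the frequency of variants with a "change in classification after reanalysis after ≥2 years", and lists the resources for the second reading as "Clinical standard laboratory software and databases in use during 2021-2022".

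The statistical methods for Objective 3 date that second reading differently: the comparison is with the "current classifications in 2020-21", assigned under the protocols of the laboratory that issued the report. The next sentence there puts the comparison "between the prenatal and 2-year postnatal classifications using chi-squared test for proportions", which suggests a clock that starts at birth. The Aims and Table 2 do not say where the clock starts.

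The inclusion criteria admit any "Prenatal CMA result reported in a singleton pregnancy during January 2013 - December 2019" (inclusive). No section limits Objective 3 to earlier reports or sets a minimum interval for each variant.

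**The concern.** The read date does two jobs in this objective. It fixes which databases and software inform the new classification, and it fixes the elapsed time that defines the outcome. Two different windows therefore mean two different versions of the measurement.

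The earlier window also sits close to the end of the report period. A variant reported in 2019 and read early in 2021 has had less than two years for evidence to accumulate. Counting it under a label of two or more years would misdescribe the proportion, and would probably understate reclassification among recent reports. The Discussion cites a US prenatal cohort in which VUS fell from 94 to 35 on reanalysis after three years, so elapsed time plausibly matters. The Translation plan anticipates offering parents reanalysis once the child is two, so this interval is one the study means to carry into practice.

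**Working it through.** **Inputs**
- Reading window: 2020-21 (statistical methods, Objective 3) or 2021-2022 (Table 2, Outcome 3).
- Minimum interval: two years (Aims; Table 2).
- Eligible reports: January 2013 to December 2019 (Inclusion criteria), which is 7 × 12 = 84 months, or 2,556 days.
- VUS in the frame: 85 per year (Sample size), so 85 × 7 = 595.
- Expected VUS participants: 267 (Sample size).
- Assumption: reports are spread evenly over the period.
- Assumption not in the documents: 12 to 26 weeks from report to birth.

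The plan gives no figure of its own to reproduce, so the check is calendar arithmetic.

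**Counted from report.** At a given read date, the latest report with two full years is the read date minus two years. The share short is the number of months from that point to December 2019, divided by 84.

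| Read date | Months short | Share | Of 595 | Of 267, same share |
|---|---|---|---|---|
| 1 January 2021 | 12 | 12/84 = 14% | 85 | 38 |
| Mid-2021 | 6 | 6/84 = 7% | about 42 | 19 |
| 31 December 2021 | 0 | 0% | 0 | 0 |

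A read during 2020 would leave all 2019 results short and some of 2018 as well. At 1 July 2020, for example, the share is 18/84 = 21%.

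A report of 31 December 2019 has 1.0 year at 31 December 2020, 1.5 years at 30 June 2021 and exactly 2.0 years at 31 December 2021. If 2020-21 means calendar years, the rule can be met, but only if each 2019 result is read on or after its own second anniversary in 2021. If it means a July-to-June year, the window closes on 30 June 2021 and the results reported after 30 June 2019 (7%) cannot reach two years.

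**Counted from birth.** At 31 December 2021, the last possible day of the window:
- 12-week gap: reports after 8 October 2019 are short; 84/2,556 = 3.3%, about 20 of 595.
- 26-week gap: reports after 2 July 2019 are short; 182/2,556 = 7.1%, about 42 of 595.

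A child from a 31 December 2019 report turns two between 24 March and 30 June 2022, which is outside 2020-21 on either reading of those years.

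**The other window.** At 1 January 2021, a report of 31 December 2019 has 1.0 year. By 31 December 2022 it has 3.0 years. The 2021-2022 window can satisfy the rule for every eligible result, from report or from birth, but only if the latest results are read late enough. Replacing the years does not secure this by itself.

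**The case against.** A reader might infer that the 2020-21 window makes two years impossible for the latest results. The documents do not support that without conditions. With calendar years and a clock that starts at the report, a December 2019 result just reaches two years in December 2021, inside the window. Impossibility holds only if 2020-21 is a July-to-June year, or for late-2019 reports if the two years run from birth.

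A reader might also infer that the plan will count variants read too early. No section says so. The two-year minimum is part of the stated outcome and can be read as governing when each variant is read. The fair criticism is that the window does not ensure the minimum.

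Three points on size also stand:
- A January 2020 read would leave 24/84 = 29% short, but it predates registration in April 2020. The article, submitted in May 2021, still puts the comparison in the future, so reads from mid-2021 onward are the realistic ones.
- The 595 is the frame. Table 2 speaks of participants in the reanalysis group, and 267 VUS participants are expected.
- Long intervals are no defect, because two or more years allows them by design.

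Objective 3 is described as a descriptive analysis, the two windows share 2021, and reports to the end of 2017 meet the from-report rule at any date in either window. These points limit the reach of the problem. They do not reconcile the two dates or say where the clock starts.

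**Conclusion.** The point holds in a limited form. The article dates one measurement in two ways, and the date is part of the outcome's definition, so this is more than a clerical slip. The shortfall is confined to the latest part of the cohort. Counted from report, it is at most 7% for reads from mid-2021 and falls to nothing at the end of that year. Counted from birth, 3 to 7% remain short even then.

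These shares rest on an even spread of reports. The from-birth figures also rest on the assumed gap of 12 to 26 weeks, and the participant counts assume that recruitment does not vary by report year. The downward direction of any bias is an inference. The documents give no reclassification rate by interval, so its size cannot be computed.

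**What to change.** - State the same reading window in the statistical methods for Objective 3 and in Table 2.
- Say whether the two years run from the prenatal report or from birth, and word the Aims, Table 2 and the analysis to match.
- Require each CNV to reach that minimum before it is read. This is needed whichever years are chosen, because 2021-2022 also opens only one year after December 2019.
- Record the interval for each CNV, so that compliance can be shown.

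The cost is a few lines of wording, plus ordering the laboratory reads so that the latest reports are done last. If the clock starts at birth, the last reads would fall between about late March and the end of June 2022 at the earliest, under the assumed gap.

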**Methods:**

This study will establish and follow up a cohort of mother-child pairs who have had a prenatal diagnosis with a chromosomal microarray from 2013-2019 in the Australian state of Victoria. Children aged 12 months to 7 years will be assessed using validated, age-appropriate measures. The primary outcome measures will be the Wechsler Preschool and Primary Scale of Intelligence IV (WPSSI-IV) IQ score (2.5 to 7 year old’s), the Ages and Stages Questionnaire (12-30 months old), and the Brief Infant- Toddler Social and Emotional Assessment (BITSEA) score. Clinical assessment by a pediatrician will also be performed. Secondary outcomes will be scores obtained from the: Vineland Adaptive Behavior Scale, Maternal Postnatal Attachment Questionnaire, the Vulnerable Child Scale, Profile of Mood States, Parent Sense of Competence Scale. A descriptive analysis of the reclassification rates of CNVs after ≥2 years will be performed.

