### Sample size

The VPDD from 2013-2019 has recorded an average of 147 CNVs (85 VUS, 62 pCNVs) each year. Our total potential CNV cohort for the proposed 7-year study period will be approximately 1029.

We expect losses of potential recruits due to failed contact tracing, language ineligibility, perinatal loss, and refusal of consent, and therefore conservatively estimate a final sample size of 354 women for the CNV cohort. This is based on 45% recruitment of women with fetal VUS (n=267), and 20% recruitment rate for pathogenic CNVs (n=87). This is in line with participation rates in the NICHD microarray cohort where they achieved 41%, 56% and 70% participation rates for those with pathogenic, VUS or benign/normal CMA results respectively [16]. There are 7155 potential eligible controls in the study period. We will require 5% of women with normal CMA results to be recruited to form the control cohort (n=358).

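### Objective 3 tests two classifications of the same CNVs with an unpaired chi-squared test, which is uninformative or miscalibrated depending on the reanalysis set, and its status and dates conflict with the rest of the article

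*Protocol article*

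**What the plan says.** Four places in the protocol article bear on this.

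- **Aims, third aim:** the target is the proportion of CNVs "reclassified from unknown or uncertain to benign or pathogenic after two or more years". This is a single proportion with prenatal VUS as its denominator.
- **Abstract, Methods:** "A descriptive analysis of the reclassification rates of CNVs after ≥2 years will be performed".
- **Table 2, Outcome 3 (Data collection):** the frequency of "copy number variants that have a change in classification after reanalysis after ≥2 years will be presented in a descriptive analysis". The population in that row is "Children who were prenatally diagnosed with a copy number variant of uncertain or unknown significance", and the software and databases are those in use during 2021-2022.
- **Objective 3 (Statistical methods of analysis and power calculations):** "We will compare the classifications given at the time of issue of the prenatal report and the current classifications in 2020-21", followed by "The proportion of pCNVs, VUS and benign variants will be compared between the prenatal and 2-year postnatal classifications using chi-squared test for proportions".

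No alpha, power or sample size is given for Objective 3. Testing runs from January 2013 to December 2019 (Study design; Inclusion criteria).

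**The concern.** A chi-squared test for proportions assumes that the two sets of observations are independent. Here each CNV appears in both, once with its prenatal class and once with its current class. The test sees only the two margins and discards the information that matters, namely which CNVs moved and where to.

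The article also leaves the reanalysis set open. Table 2 and Aim 3 point to VUS only. The Objective 3 sentence lists pathogenic, VUS and benign variants at both times, which could mean all CNVs. The test fails under either reading, but differently.

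Two further conflicts sit in the same sentences: a hypothesis test against an analysis elsewhere called descriptive, and "the current classifications in 2020-21" against 2021-2022 in Table 2. At stake is the result for one of three stated aims, which is meant to inform recommendations on offering reanalysis after two years.

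**Working it through.** The plan gives no figure for Objective 3 to reproduce. The expected numbers do reproduce from the Sample size section: 7 × 85 × 0.45 = 267.75 (stated 267 VUS) and 7 × 62 × 0.20 = 86.8 (stated 87 pCNVs), 354 in all. A two-sided 5% level is assumed below.

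**Reading 1: only prenatal VUS are reanalysed, n = 267.** The prenatal row is 267 VUS, 0 pathogenic, 0 benign. Suppose k are reclassified, a to benign and b to pathogenic, with a + b = k. Across the two rows the benign column contributes a, the pathogenic column b, and the VUS column k²/(2n − k). The statistic is

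k + k²/(2n − k) = 2nk/(2n − k).

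The split between benign and pathogenic drops out. The statistic is a function of k alone, on 2 df if both new classes occur and on 1 df if only one does.

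| k | k/267 | statistic | p, 1 df | p, 1 df, continuity-corrected | p, 2 df (exp(−statistic/2)) | exact McNemar (2 × 0.5^k) |
|---|---|---|---|---|---|---|
| 4 | 1.5% | 534 × 4/530 = 4.03 | 0.045 | 0.132 | 0.133 | 0.125 |
| 6 | 2.2% | 534 × 6/528 = 6.07 | 0.014 | 0.040 | 0.048 | 0.031 |

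Equality of the margins is false as soon as one VUS moves, so the p-value adds nothing to k/n. McNemar is no remedy here, since every move leaves VUS and it too is fixed by k. The informative quantity is the proportion with an exact interval: 27/267 = 10.1% (6.8% to 14.4%), or 53/267 = 19.9% (15.2% to 25.2%).

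**Reading 2: all CNVs are reanalysed, N = 354.** Collapse to pathogenic versus not, with prenatal p = 87/354 = 0.246. The unpaired test uses a variance for the difference of 2p(1 − p)/N = 0.371/N. Under equal margins the true variance is d/N, where d is the share of CNVs that change class. For d = 0.20 the effective critical value is 1.96 × √(0.371/0.20) = 2.67, a true size of about 0.008. Simulation (20,000 runs) agrees:

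- True size with 5%, 10%, 20% and 30% discordant: 0.000, 0.000, 0.008 and 0.030. McNemar: 0.050 to 0.053.
- Power, unpaired against McNemar: 3% v 90% (5% up, 1% down), 36% v 97% (8% up, 2% down), 58% v 97% (10% up, 3% down).

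**What margins hide.** The Discussion cites a reanalysis in which VUS went from 94 to 35, pathogenic from 35 to 70 and likely benign from 36 to 60. Unpaired chi-squared is 44.7 on 2 df (p = 2 × 10⁻¹⁰), but it counts 165 CNVs as 330. The margins show only that at least 94 − 35 = 59 CNVs moved, not how many did.

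**Dates.** Assume testing uniform over the seven years and the interval counted from the prenatal test. The share under two years old is then 1.5/7 = 21% at mid-2020, 1/7 = 14% at January 2021, 0.5/7 = 7% at mid-2021 and 0% at end-2021. Over those dates the interval runs from about half a year (December 2019 to mid-2020) to almost nine years (January 2013 to end-2021), so the label of a 2-year classification does not describe it.

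**The case against.** The strongest reply is that Aim 3 is already served. The abstract and Table 2 both promise a descriptive reclassification rate, Objective 3 has no power claim, and the chi-squared sentence is an addition that decides nothing else in the study. This stands, and it limits the severity. A reader might infer that the plan fails to estimate Aim 3; the documents do not support that.

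A reader might also infer a dramatic distortion of the p-value. With 20 upgrades and 2 downgrades among 354 CNVs, the unpaired test on pathogenic versus not (87 v 105) gives p = 0.13, while exact McNemar gives 0.0001. That contrast needs all CNVs reanalysed, two categories instead of the planned three, and no VUS becoming benign. Adding 10 VUS-to-benign moves (87/267/0 v 105/239/10) gives 18²/192 + 28²/506 + 10 = 13.2 on 2 df, p = 0.001. In the VUS-only set the chi-squared and exact paired tests broadly agree beyond very small counts. The contrast shows what can happen, not what to expect.

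A third tempting inference is that CNVs under two years old will be included and will lower the rate. The abstract, Aim 3 and Table 2 all require two or more years, so such CNVs may be excluded or reanalysed late in the window. A downward pull is plausible but nothing in the article shows it. What stands is the conflict between the dates and the possibility it leaves open.

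**Conclusion.** The point holds. The named test is wrong for paired data under either reading of the reanalysis set. With VUS only, it is uninformative, because the p-value is a function of the number reclassified. With all CNVs, it is conservative and weak in the binary comparison, with size 0.000 to 0.030 in place of 0.05 and power of 3% to 58% where McNemar has 90% to 97%. Those figures rest on the expected 354 CNVs, the collapse to two categories and the assumed movement rates.

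The sentence is also inconsistent with the descriptive status given elsewhere, and the 2020-21 and 2021-2022 windows must be reconciled. Between 0% and 21% of tests could fall short of two years, depending on the reanalysis date and assuming uniform testing.

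Harm is confined to Objective 3. All classifications remain available for a correct cross-table, so this is a should-fix item.

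**What to change.** - Delete the chi-squared test from Objective 3, in line with the descriptive analysis in the abstract and Table 2.
- State the reanalysis set: prenatal VUS only, or all CNVs.
- Report the proportions of prenatal VUS reclassified to benign and to pathogenic, each with an exact 95% CI, and the full prenatal-by-current cross-table.
- If pathogenic CNVs are also reanalysed and a test is wanted, use exact McNemar on pathogenic versus not pathogenic. A three-category paired test such as Stuart-Maxwell is not a clean substitute: pre-screening stage 1 sorts CNVs into pathogenic and VUS only (62 + 85 = 147 a year), so the prenatal benign category is empty by construction.
- Give one date window throughout, count only CNVs whose current classification is made at least 24 months after the prenatal report, and replace the 2-year label with the actual interval. Table 2's 2021-2022 window makes this possible for every CNV but does not by itself guarantee it.

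The cost is a few sentences and one harmonised window, with no new data. The one downside is that reanalysis of the late-2019 tests must wait until their 24 months have passed, which for December 2019 reports means December 2021.
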